## Abstract

**Introduction:**

Up to 30% of hearing aids fitted to new adult clients are reported to be of low benefit and used intermittently or not at all. Evidence suggests that additional interventions paired with service-delivery redesign may help improve hearing aid use and benefit. The range of interventions available is limited. In particular, the efficacy of interventions like the Active Communication Education (ACE) programme that focus on improving communication success with hearing-impaired people and significant others, has not previously been assessed. We propose that improved communication outcomes associated with the ACE intervention, lead to an increased perception of hearing aid value and more realistic expectations associated with hearing aid use and ownership, which are reported to be key barriers and facilitators for successful hearing aid use. This study will assess the feasibility of delivering ACE and undertaking a definitive randomised controlled trial to evaluate whether ACE would be a cost-effective and acceptable way of increasing quality of life through improving communication and hearing aid use in a public health service such as the National Health Service.

**Methods and analysis:**

This will be a randomised controlled, open feasibility trial with embedded economic and process evaluations delivered in audiology departments in two UK cities. We aim to recruit 84 patients (and up to 84 significant others) aged 18 years and over, who report moderate or less than moderate benefit from their new hearing aid. The feasibility of a large-scale study and the acceptability of the ACE intervention will be measured by recruitment rates, treatment retention, follow-up rates and qualitative interviews.

**Ethics and dissemination:**

Ethical approval granted by South East Coast-Surrey Research Ethics Committee (16/LO/2012). Dissemination of results will be via peer-reviewed research publications both online and in print, conference presentations, posters, patient forums and Trust bulletins.

**Trial registration number:**

ISRCTN28090877.

Strengths and limitations of this studyThis will be the first study to evaluate the processes involved in delivering the Active Communication Education (ACE) intervention in a general practitioner referral pathway for new National Health Service hearing aid users.If the randomised controlled trial (RCT) is shown to be feasible then the data from this study will provide critical information that will inform the design of a larger RCT to determine the social, clinical and economic outcomes of the ACE in this important clinical pathway.The study is powered to allow the SD of the proposed outcome measures to be estimated with reasonable certainty to inform future sample size calculations.This study is limited to assessing the feasibility of RCT and ACE delivery processes. Ultimately, the test of whether the ACE intervention leads to long-term communication success, better hearing aid use, hearing aid benefit, quality-of-life and economic gains, will be tested in a future full-scale RCT.

## Introduction

Age-related hearing impairment is a major worldwide public health issue for ageing populations.^1^ It is reported as the third most common chronic condition affecting approximately 328 million (91%) middle-aged and older adults,^2^ over 10 million adults in the UK alone.^3 4^ By the age of 70, 70% will have a mild or worse hearing impairment, progressively worsening with age.^5^ Hearing impairment is commonly associated with reduced quality of life and well-being^6–8^ including depression^9^ and anxiety,^10^ social isolation,^8^ poor social interactions,^11–13^ cognitive dysfunction,^14^ increased risk of developing dementia and reduced emotional, behavioural and general social well-being.^15^ In addition, disability in these domains is often experienced by normally hearing significant others (SOs) living with hearing-impaired people.^16–18^ Hearing impairment therefore represents an enormous burden on society and the economy.

In high-income countries, the most common treatment is to fit a hearing aid.^6^ Despite strong evidence that hearing aid use is associated with reductions in hearing disability noted above,^6 19–21^ hearing aid use is remarkably low.^22 23^ It is estimated that up to 30% of UK adult hearing aid owners do not use them regularly or at all.^4 24–26^ International studies support these data.^8 27–29^ Cost implications for the National Health Service (NHS) are significant as they provide 80% of UK hearing aids,^25^ fitting >300 000 new devices each year of which an estimated 20 000–120 000 are unused. Even with global advances in technology, fitting protocols and outcome measurements,^30^ there is little evidence that NHS hearing aid use and the expected gains in benefit and quality of life have improved over the last decade^19 25^ and treatment continues to focus primarily on technology.

A recent systematic review of additional treatment found very low quality evidence that self-management and service delivery interventions may be of benefit in auditory rehabilitation.^31^ However, the authors found no studies that examined the effect of these sorts of interventions on hearing aid use.

Reasons for hearing aid non-use are complex.^32^ Research has identified psychosocial factors important for successful aural rehabilitation including personal and societal attitudes to hearing-impairment^33^ patient involvement in decision making^34–37^ and expectations of benefit and communication success in a range of communication situations.^38 39^ Key barriers and facilitators to successful hearing aid use have been identified as being related to expectations of benefit and meaningful participation in everyday life.^40 41^ The WHO’s International Classification of Functioning, Disability and Health^42^ provides a functional description of difficulties (related to these expectations) experienced by hearing-impaired people and their hearing communication partners, for example, avoidance of difficult listening situations that lead to ‘activity limitations’ and ‘participation restrictions’.

One intervention that is designed to reduce these limitations and restrictions is the Active Communication Education (ACE) programme (the focus of this paper). The ACE trains participants to develop solutions to specific difficult communication scenarios that commonly lead to their avoidance of or reduced participation in important activities. The effectiveness of ACE as an *alternative* intervention to a hearing aid has been evaluated and two small studies demonstrate ACE benefits in improving communication function and hearing-related quality of life.^43 44^ ACE effectiveness as an *adjunct* to hearing aid fitting has not been evaluated, although there is some weak evidence that supports its use in this context,^43^ that is, long-term improvements in using communication strategies being associated with hearing aid users.

A systematic review of group communication programme effectiveness conducted in 2005,^44^ revealed just nine small and methodologically poor studies. The review reported weak evidence for short-term benefits related to reduced hearing disability; improvements in quality of life; hearing aid use and communication function^45^ when interventions were delivered in concert with a hearing aid. The authors concluded that there was a clear need for large sufficiently powered randomised controlled studies to determine short-term and long-term benefits of adult communication rehabilitation group interventions as an adjunct to hearing aid fitting. Such a study has yet to be completed. Evidence that postdates this 2005 review does little to change the situation providing only weak additional evidence for moderate gains in hearing loss-related quality of life for communication-based group interventions.^46^ There are indications that group rehabilitation programmes like ACE have the potential to realise economic gains for service providers. For example, Abrams^47^ estimated that a hearing aid plus a 4-week group rehabilitation programme reduced the treatment cost per quality-adjusted life-year (QALY) gained by more than half; the cost of implementing the rehabilitation programme was <6% of the total rehabilitation cost per patient. Even so, with no strong evidence that such interventions delivered as an adjunct to hearing aid fitting are clinically worthwhile, they are not routinely offered in public or private hearing healthcare sectors in the UK.

In summary, there is some low-quality evidence that ACE and similar programmes improve communication function and quality of life and these outcomes may be enhanced when delivered in conjunction with a hearing aid. Communication programmes involve a substantial commitment on the part of participants and those who run and pay for them. Recent evidence shows that it is effective and feasible to deliver ACE as an alternative intervention in Australia and Sweden.^43 48–50^ There is now a need to establish whether reported clinical and economic benefits of ACE and communication programmes like ACE can be achieved in the context of NHS hearing aid provision. This protocol for The ACE to HEAR study (ACEto improve HEARing) is intended to deliver ACE to unsuccessful or struggling new NHS hearing aid users, 3 months postfitting, in order to assess whether a large RCT designed to evaluate the effectiveness of ACE in improving hearing aid benefit within the UK NHS is feasible.

## Methods and analysis

This protocol was developed and is reported according to the Standard Protocol Items for Randomised Trials statement.^51^

### Study aim

The aim of this study is to determine the feasibility of delivering a future, full-scale randomised controlled trial (RCT) to evaluate ACE plus treatment-as-usual versus treatment-as-usual alone, within the UK NHS in two UK cities. Treatment-as-usual is defined as a referral from a patient’s GP to audiology services to treat permanent hearing loss. It comprises up to two appointments for hearing aid fitting and a third face-to-face or telephone follow-up appointment.

### Study objectives

Objectives will evaluate ACE delivery and trial delivery processes.

#### ACE delivery objectives

To assess ACE uptake rates, eligibility and acceptability of clinic location (between and within the two study sites) for participants and SOs.To evaluate the level of ACE attendance and retention among participants randomised to the ACE arm of the study.To assess acceptability of ACE with participants, SOs and audiologists.To assess capability, capacity and willingness of audiology departments to support delivery of ACE within existing services.To assess intervention fidelity of delivering ACE.

#### Trial delivery objectives

To assess RCT recruitment rates, evaluate the randomisation process and time to accrue ACE groups.To assess the acceptability of study processes to participants, SOs and audiologists (ie, those related to recruitment, the feasibility of identifying struggling hearing aid users, randomisation process, data collection, measurement of ACE fidelity and acceptability).To explore patient-reported outcome measures (PROMs) and estimate likely SD, including quality-of-life tools (EQ-5D-5L; Short-Form 36 (SF-36)) and a bespoke healthcare resource use/acceptability/utility questionnaire for use in an intended full-scale RCT.

### Study design

This study commenced on 1 February 2017 and is of 24 months duration. The study design is a randomised controlled, open feasibility trial with embedded economic and process evaluations delivered in one audiology department in each of two UK cities. The design of the trial is shown in figure 1.

**Figure 1 F1:**
[figure not shown]
ACE to HEAR study flow diagram. The diagram was developed using Consolidated Standards of Reporting Trials guidelines (http://www.consort-statement.org/) and indicates the main processes of the trial, their relationship with the outcome measures and their timing. ACE, Active Communication Education; IOI-HA, International Outcomes Inventory for Hearing Aids; IOI-HA-SO, IOI for hearing aids: version for SO; IOI-AI, International Outcomes Inventory for Alternative Interventions; IOI-AI-SO, IOI for Alternative Interventions: vwesion for SO; SAC, Self-Assessment of Communication; SF-36, Short-Form 36; SO, significant other; SOS-HEAR, Significant Other Scale for Hearing Disability.

### Study setting

Study sites for this feasibility study are the Audiology Departments at York Hospital (YH), York Teaching Hospitals NHS foundation Trust and the Bradford Royal Infirmary (BRI), Bradford Teaching Hospitals NHS Foundation Trust.

### Study population

The study population will consist of adult patients aged 18 years or over, receiving treatment-as-usual delivered in one of the two participating centres. They will be considered potentially eligible if all of the following eligibility criteria apply at their 3-month postfitting follow-up appointment.

### Inclusion criteria

Moderate or less than moderate benefit, defined by International Outcomes Inventory for Hearing Aids (IOI-HA) question 2.^52 53^
Hearing impairment: pure-tone average better ear thresholds at 500, 1000, 2000 and 4000 Hz of >25 dB HTL.No significant self-reported history of neurological impairment.Willing to provide written informed consent.Able to provide written informed consent.Able to take part in the intervention by understanding and using spoken English.Able to self-complete the English language outcome measure tools.The following inclusion criteria for SOs will be assessed:A spouse or other family member who lives with or is a carer for a patient recruited to the study.

### Exclusion criteria

Severe or profound bilateral hearing impairment. Pure-tone better ear average thresholds measured at 500, 1000, 2000, and 4000 Hz of >85 dB Hearing Threshold Level (HTL), since experience^48^ suggests this group of patients may struggle to effectively participate in the intervention setting.Significant ongoing ear-related health or mental health issues that, in the audiologist’s or associate audiologist’s professional opinion, would preclude hearing aid fitting or attendance at ACE sessions.Unable or unwilling to give written informed consent.

In addition, SOs will be excluded if they are unable or unwilling to give written informed consent.

Patients who do not have a SO or family member able to attend the ACE sessions are still eligible to participate in the study.

### Sample size calculation and recruitment

As this is a feasibility study, the main purpose is to assess the acceptability and feasibility of conducting this study, with a view to designing and conducting a future full-scale trial.^54^ Six ACE groups are planned with up to seven patients in each (five minimum). This leads to a maximum sample size of 44 patients and up to 44 SOs for the ACE intervention arm, and 44 in the control arm (n=88). This sample size will allow the SD of the proposed outcome measures to be estimated with reasonable certainty to inform future sample size calculations.^54^ Collectively, the two study sites fit approximately 4300 hearing aids a year and based on their experience we estimate 10% will require extra help at follow-up and be eligible for inclusion. Recruitment of patients commenced on 1 April 2017 and is now underway. The recruitment window is currently planned to end on 28 February 2018 and there is potential to extend this phase until 30 April 2018 if necessary.

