### Randomisation

Eligible, consenting patients from the same study site who have completed baseline assessments will be randomised by a remote, centralised randomisation service (provided by York Trials Unit) in batches of 10–14 (intervention:control ratio of 1:1) using block randomisation in a single large block per batch. Following randomisation, a letter outlining the next steps will be sent to participants. For those allocated to the ACE arm, this will contain an invitation for them and their SO to attend five ACE sessions, including details of the venue, times and information.

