## Conclusion

This will be the first RCT of this type of group communication programme in the context of a public health service and as an adjunct to hearing aid fitting. The impact of this study will ultimately be realised by a larger fully powered RCT designed to determine the effectiveness of the ACE intervention in improving hearing aid benefit for hearing aid users within the NHS GP referral for a hearing aid pathway in the UK. The outcomes of this study will inform such a RCT.

The feasibility study will be deemed successful if:Seventy per cent of recruitment targets attained for all research components.Study consent/retention rates and proposed sample sizes, indicate delivery of the full RCT is plausible within a 5-year study period.Ninety per cent of ACE groups of five to seven consented participants formed within the intervention window with participants attending three of five sessions.Economic, acceptability, outcome measure and fidelity evaluation data successfully collecteParticipants, SOs and audiologists evaluate acceptability of the ACE and RCT positively.

(Measures with over 10% missing data maybe modified/replaced prior to the main trial).

The criteria for success will result in one of following outcomes:stop: full-scale RCT not be feasible in NHS setting;continue: feasible with modifications;continue: feasible with no modifications, close monitoring;continue feasible as is.

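### The stated maximum sample size (44 per arm, 88 in total) does not follow from six groups of up to seven, which give 42 per arm and 84 in total, so the patient threshold for the 70% recruitment criterion is unclear

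*Protocol article*

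**What the plan says.** The section on sample size and recruitment sets out the group structure: "Six ACE groups are planned with up to seven patients in each (five minimum"). From this it draws its total: "This leads to a maximum sample size of 44 patients and up to 44 SOs for the ACE intervention arm". The same sentence then gives an equal number of controls and an overall total of 88 patients. It presents the total as a consequence of the group structure and mentions no allowance for dropout or over-recruitment.

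The abstract gives a different figure: "We aim to recruit 84 patients (and up to 84 significant others) aged 18 years and over".

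The Randomisation section states that patients are allocated "in batches of 10–14 (intervention:control ratio of 1:1) using block randomisation in a single large block per batch".

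The Conclusion lists five conditions for calling the feasibility study successful. The first is "Seventy per cent of recruitment targets attained for all research components". It names no number of patients. The list is followed by four graded outcomes, from stopping to continuing unchanged.

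**The concern.** The planned sample size is a headline figure, and the article gives two values for it. One of them is not the product of the numbers from which it is said to come. In a feasibility trial, attainment of the recruitment target is itself a result, so the target needs a single value. Recruitment was already under way when the article was written, so the figure should be settled before the final count is known. Otherwise the choice between 84 and 88 could be made after seeing which one is met.

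**Working it through.** **Inputs**

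- Number of ACE groups: 6 (sample size section).
- Patients per group: 5 to 7 (sample size section; the Conclusion gives the same range).
- Allocation 1:1, batches of 10 to 14 (Randomisation).
- Stated totals: 44 + 44 = 88 (sample size section); 84 (abstract).
- Recruitment criterion: 70% of target (Conclusion).

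**Step 1. Reproduce the stated maximum**

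ACE arm maximum = groups × cap = 6 × 7 = 42. With 1:1 allocation, total = 2 × 42 = 84. The stated 44 and 88 are not reproduced. The minimum is 6 × 5 = 30 per arm and 60 in total, so the stated rules allow 60 to 84 patients.

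**Step 2. Cross-check with the batches**

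One batch supplies one ACE group and its controls: 14 / 2 = 7 and 10 / 2 = 5. If there are six batches, one per group, the maximum is 6 × 14 = 84.

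**Step 3. Look for a reading that gives 44**

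- Six groups holding 44: 44 / 6 = 7.33 per group, so at least one group would need eight or more, above the cap.
- Groups of seven: 44 / 7 = 6.29 groups, which is not six.
- Dropout inflation: 42 / (1 − 0.04) = 43.75, rounded up to 44, and 84 / (1 − 0.04) = 87.5, rounded up to 88. This needs an allowance of about 4%, and the article states none.

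The calculation is an exact product of whole numbers, so rounding cannot explain the difference.

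**Step 4. Effect on the 70% criterion**

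0.70 × 84 = 58.8, so 59 patients. 0.70 × 88 = 61.6, so 62 patients.

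| Patients recruited | % of 84 | % of 88 |
|---|---|---|
| 58 | 69.0 | 65.9 |
| 59 | 70.2 | 67.0 |
| 60 | 71.4 | 68.2 |
| 61 | 72.6 | 69.3 |
| 62 | 73.8 | 70.5 |

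The two targets disagree only at 59, 60 and 61. Sixty is the number reached if all six groups form at the minimum permitted size with equal controls (6 × 5 × 2).

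**Step 5. Effect on precision of the SD**

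The section justifies the size by precision of the SD, and the analysis section reports SDs with 80% CIs. The limits, as multiples of the observed SD, are √[(n − 1)/χ²(0.90; n − 1)] and √[(n − 1)/χ²(0.10; n − 1)], assuming normal data with none missing.

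- All patients: 0.912 to 1.113 at n = 84; 0.913 to 1.110 at n = 88.
- One arm: 0.880 to 1.171 at n = 42; 0.882 to 1.166 at n = 44.

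The differences are negligible.

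**The case against.** The arithmetic cannot be defended, but the consequences can be disputed.

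- **Which figure is the target.** The abstract is the only place that states a recruitment aim, while the sample size section calls its figure a maximum. A careful reader would probably take 84. This stands, and it is a reason to choose 84 in the correction. It does not remove the ambiguity, because the Conclusion refers only to targets and the section devoted to sample size says 88.
- **The batch check is not fully independent.** The Randomisation section does not give the number of batches; six is carried over from the number of groups. This also stands. The error is established by 6 × 7 and by the abstract without it.
- **Size.** Only three possible results are affected, and neither the design nor the analysis changes. This stands.

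A reader might infer that the trial has a go/no-go rule with two values. The article does not support that: recruitment is one of five criteria, the outcomes are graded, and nothing ties a miss on this criterion to stopping.

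A reader might also infer that every recruitment percentage in the report is affected. The recruitment outcomes and the analysis section describe counts, and referral, consent and attendance rates. Nothing there uses the planned total as a denominator.

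Finally, it is tempting to rewrite the whole criterion as 59 of 84 patients. The criterion covers all research components, which may include significant others and the interview samples, so a patient count alone would narrow it.

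**Conclusion.** The stated maximum of 44 per arm and 88 in total is wrong on the section's own inputs and conflicts with the abstract. The correct product is 42 per arm and 84 in total. The error is 2 patients per arm and 4 overall.

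It is more than a slip of the pen, because the planned size is also the likely denominator for the patient part of a prespecified success criterion, whose threshold becomes 59 or 62. The practical reach is small: only results of 59 to 61 are classified differently, and the stated purpose of estimating the SD is unaffected.

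The conclusion assumes that the cap of seven and the count of six groups are as intended. The abstract supports both.

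**What to change.** 1. In the sample size section, replace 44, 44 and 88 with 42, 42 and 84, and give up to 42 significant others for the ACE arm.
2. In the Conclusion, state that the patient-recruitment component of the 70% criterion is measured against 84, that is, at least 59 patients. Leave the criterion as it is for the other research components.

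The cost is a line of text in each place. The number of groups, the batch sizes, the allocation and the analysis do not change.
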